### 1.4. Primary Outcomes

Safety will be assessed in a binary manner as the absence of the occurrence of adverse events of grade ≥3 with a proven or reasonably conceivable causal relationship with the MD or its related procedure. Grades will be determined using the common terminology criteria for adverse events (CTCAE) classification version 5 (or 6 if available) [41]. 

Performance will be considered satisfactory if at least one of the three modules is analysable. A module will be considered analysable if (1) it is found in the faeces within a 96-h period, (2) the recovered volume of its contents is ≥25 µL, and (3) its visual condition is satisfactory (no faecal contamination).

The criteria to evaluate the secondary objectives are as follows: (1) the number and grade of adverse events notified (including response to follow-up volunteer-diaries, number of unscheduled medical visits); (2) the number of modules recovered per volunteer; (3) the volume recovered from each module (recovered volume must be ≥25 μL); (4) the pH of the recovered MD contents (a measured pH ≥5 will prove that the MD did not sample stomachal liquid where the pH is lower [42]); (5) the visual assessment of the module evaluating whether it is intact and has no visible cracks or damages that could lead to faecal contamination; (6) metabolomic and metagenomic analyses of the module contents; (7) the rating of the device (devices “acceptability”) based on the questionnaire and the end-of-participation visit with the principal investigator; and (8) the results of the culturomic analysis of the module contents, on up to two volunteers.

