## 1. Introduction

The human gastrointestinal tract (GIT) consists of various segments, each characterised by distinct environmental conditions. These environmental conditions play a direct role in shaping the microbiome of the GIT. The gut microbiome, a complex ecosystem, encompasses communities of microorganisms, including bacteria, fungi, and archaea, along with their biological components like metabolites, proteins, or free nucleic acids [1]. The human gut microbiome exhibits a stratified distribution from the duodenum to the colon, characterised by a progressive increase in bacterial density and diversity (from 10^3^ CFU/mL to 10^11^ CFU/mL) along this continuum [2]. It is well established that the human gut microbiome plays a crucial role in preserving the host’s health, directly influencing metabolic and immune homeostasis. Gut microbiome dysbiosis is characterised by a decrease in microbial diversity, the absence of beneficial microorganisms, and the potential presence of pathogenic microbes, and it can lead to alterations in the composition of gut microbiota-derived metabolites, thereby contributing to the development of various pathologies [3,4]. Numerous studies have established connections between the intestinal microbiome and conditions such as metabolic diseases, inflammatory bowel diseases, cancers, and neurological disorders [5,6,7,8,9,10]. Gut microbes exert a direct or indirect influence on the host’s physiology by regulating various hormones, neurotransmitters, or metabolites [11]. Certain metabolites, like Short Chain Fatty Acids (SCFA), are known to have direct impacts on gut physiology, exhibiting anti-inflammatory effects, maintaining the integrity of the gut barrier, and serving as the primary energy source for colonocytes [12,13,14]. These metabolites are either directly produced by gut microbes, from diet, from host metabolite such as amino-acids conjugated bile acids, or de novo [4].

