### 1.3. Aims and Objectives

The primary objective of this clinical study is to demonstrate the safety and performance of the medical device. This objective is, thus, composite and will be achieved if both the safety and the performance of the MD are observed for at least 12 out of 15 volunteers. 

Each volunteer will ingest only one pill (the MD) containing tree modules.

The secondary objectives of this study are as follows: (1) to verify the safety of use of the MD for the collection of intestinal content, (2) to verify that the MD is transiting in the human intestinal tract, (3) to evaluate the capture of intestinal liquid by the MD, (4) to verify that the MD opened in the intestine, (5) to verify the state of the MD after collection, (6) to evaluate the sample’s functional potential and identify biomarkers (microorganisms, metabolites) via metagenomics and metabolomics, (7) to estimate the volunteer’s experiences about the MD ingestion and its use, and (8) to obtain the sample’s functional potential and identify biomarkers via culturomics for two subjects.

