We predict that the medical device will be fully safe for the 15 volunteers and that no side-effects will be noticed. Moreover, we expect to achieve small intestinal liquid collection as well as to recover all modules from the faecal matter of the included volunteers. We anticipate that the volunteers’ feelings about the ingestion and use of the medical device will be positive. To perform multi-omics analysis, we presume that the volume collected by the modules will be sufficient and that samples will be analysable to determine the functional potential of each sample. We expect to find differences in profiles depending on sample origins (faecal matter vs. small intestinal liquid). The bacterial composition is expected to be more diverse and richer in faecal samples compared to small intestinal samples according to the literature [23]. In a previous clinical investigation performed with a collection module, Shalon et al. showed distinct microbial communities depending on the collection site [44]. They notably found a higher abundance of *Pseudomonadota* in small intestinal samples than in faeces and a lower alpha diversity relative to the intra-individual diversity in intestinal samples compared to faeces. We also expect to observe differences in the metabolome. In the same clinical study, Shalon et al. analysed the bile acid profiles along the intestinal tract. As a result, they obtained divers bile acid compositions with more primary bile acids (Cholic acid and Chenodeoxycholic acid) in the small intestinal samples, and faeces were dominated by secondary bile acids [44]. The culturomics analysis will allow us to isolate microbes and potentially to identify new bacteria. These bacteria could possibly be new probiotics [45].

Pelican Health is proactively addressing the burden of faeces collection imposed on volunteers in the current study by ensuring that pick-ups align with the volunteers’ way of life in this study. Currently, we are developing approaches to facilitate both the recovery of faeces and the medical device recovery from faeces, thereby lowering additional costs and patient burden. 

Sample contamination is a common issue frequently observed during the employment of other non-invasive sampling tools [46], and even during catheter aspiration [18]. However, the design and technical constraints incorporated into the development of the Pelican Health sampling device are specifically intended to limit these situations. 

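### The primary performance endpoint has no condition on where a module filled, so meeting 12/15 cannot by itself support a claim of small-intestinal sampling

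*Protocol article*

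**What the plan says.** All references are to the protocol article.

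- **Volunteer-level rule (Section 1.4).** "Performance will be considered satisfactory if at least one of the three modules is analysable".
- **Module-level rule (Section 1.4).** There are three numbered conditions: "A module will be considered analysable if (1) it is found in the faeces within a 96-h period"; "the recovered volume of its contents is ≥25" µL; and "its visual condition is satisfactory (no faecal contamination").
- **Trial-level rule (Sections 1.3 and 2.8).** The primary objective is met if safety and performance are both observed in at least 12 of 15 volunteers.
- **pH.** This is secondary criterion 4 in Section 1.4: "a measured pH ≥5 will prove that the MD did not sample stomachal liquid where the pH is lower". It serves secondary objective 4 in Section 1.3, "to verify that the MD opened in the intestine". Section 2.5 has it read with indicator paper on the supernatant after centrifugation.
- **Contamination and integrity.** Section 2.5 has modules washed and checked for leakage. Secondary criterion 5 is a visual check for cracks or damage.
- **Paired omics (Sections 2.5 and 2.6).** One module per volunteer and the matching stool undergo 16S sequencing, qPCR for bacterial load, and metabolomics.
- **Intended site and conclusion.** Section 1.2 describes a device aimed at the small intestine, with a capsule that degrades at the distal jejunum or proximal ileum. Section 3 says the investigation will show the device to be safe and effective for sampling small-intestinal liquid.

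**The concern.** The endpoint and the conclusion concern different things. The endpoint asks whether a filled, clean-looking module came out in time. The conclusion is about the part of the gut the liquid came from. The study's rationale is that stool does not represent the small intestine, so sampling site is the property that gives the device its value.

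As written, the trial could report its primary objective as met on modules that filled in the stomach or the colon, and nothing in the primary result would show it. The gastro-resistant capsule is a design intention. In the device's first evaluation in volunteers it needs checking and cannot itself serve as evidence of site.

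**Working it through.** The plan states no power, alpha or expected rate for this endpoint, and Section 2.7 sets 15 volunteers on feasibility. There is therefore no figure to reproduce. The main check is a reading of each criterion against three possible filling sites.

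| Criterion | Role | Excludes stomach? | Excludes colon? |
|---|---|---|---|
| Found within 96 h | primary | no | no |
| At least 25 µL | primary | no | no |
| Visually clean | primary | no | no; addresses visible faecal contamination only |
| pH ≥5 | secondary 4 | yes, as the plan argues | no; lower bound only |
| No visible cracks or damage | secondary 5 | no | no; addresses leakage only |
| Paired 16S, qPCR, metabolomics | secondary 6 | not directly | informative, but no stated role in the definition of analysable |

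The three primary rows are the complete definition. A module that filled in the stomach or colon, was found in time with 25 µL and looked clean passes all three.

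The last row can inform on site. Section 3 expects "more primary bile acids (Cholic acid and Chenodeoxycholic acid) in the small intestinal samples, and faeces were dominated by secondary bile acids". Module content close to the volunteer's own stool would point to colonic filling or contamination. A difference from stool would not alone establish small-intestinal origin, since gastric content could differ too. That is why pH and the paired comparison are needed together.

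**Illustration of what a site condition could change.** The rates below are assumptions, since the documents give none.

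- q = probability that a volunteer meets the primary endpoint as written (safety and performance together).
- f = share of those volunteers whose analysable modules are all off target.
- As written: P(X ≥ 12), with X ~ Binomial(15, q). This does not depend on f.
- With a perfect site check: P(X ≥ 12), with X ~ Binomial(15, q(1 − f)).

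| q | as written | f = 10% | f = 20% | f = 30% | f = 50% |
|---|---|---|---|---|---|
| 0.90 | 0.944 | 0.685 | 0.358 | 0.135 | 0.006 |
| 0.95 | 0.995 | 0.838 | 0.498 | 0.205 | 0.011 |

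For example, q = 0.90 and f = 20% give 0.90 × 0.80 = 0.72 per volunteer, and P(X ≥ 12) = 0.358. A pH condition would catch only the gastric part of f, so the table shows the most that a site check could change, not what pH ≥5 alone would do.

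**The case against.** The best reply is that ranking endpoints is a design choice. In a 15-person pilot a technical primary outcome is reasonable, and Section 1.3 gives opening in the intestine and sample content their own secondary objectives. This stands: the placement is not in itself an error. It does not remove the gap, because Section 3 draws a conclusion about site that the primary endpoint cannot carry.

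A reader might infer stronger points that the documents do not support.

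- **That the plan wrongly claims pH ≥5 shows small-intestinal origin.** The sentence claims only that stomach liquid was not sampled. It says nothing about the colon, so there is no false statement to correct there.
- **That colonic filling or leakage goes wholly unexamined.** Leakage and integrity are inspected, a leaking module is replaced by a back-up for the omics, and each analysed module is paired with stool. The supportable point is that the paired omics do not feed into the primary endpoint.
- **That an invisible leak would swamp the sample.** The Introduction gives a "progressive increase in bacterial density and diversity (from 10^3^ CFU/mL to 10^11^ CFU/mL") running from duodenum to colon. An assumed 1 nL leak at 10^11 CFU/mL carries 10^5 cells. Against 25 µL of content at 10^6, 10^7, 10^8 or 10^9 CFU/mL (2.5×10^4 to 2.5×10^7 cells), its share is 80%, 29%, 3.8% or 0.4%. The lower density quoted belongs to the duodenum, not to the device's target segment. The leak size and the densities used here are assumptions. No size can be claimed.
- **That the device does sample off target.** No rate is given, and the table above is no evidence of one.
- **That the article should state a molecular pass/fail rule.** Section 2.8 sets the multi-omics apart from the descriptive analyses, and such detail may sit in the full protocol or analysis plan. Its absence here is not a finding.

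**Conclusion.** The point holds in a limited form. The primary performance definition is stated in full and contains no condition on sampling site. Meeting 12/15 therefore shows recovery of a sufficiently filled module that looks clean, and does not show that small-intestinal liquid was sampled. pH is outside the definition and addresses the stomach alone, and no stated criterion separates small intestine from colon.

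This follows from the text and needs no assumed rates. The size of the effect is unknown because the documents give no off-target rate. The binomial figures show only that the rule as written cannot respond to sampling site, and that modest off-target shares would matter if it did. The change is worth making because it alters what the trial may conclude.

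**What to change.** 1. **Second report of the primary proportion.** Pre-specify that the result out of 15, with its threshold of 12, is also reported with an analysable module required to have pH ≥5. Section 2.5 reads as though pH is taken on each recovered module; if it is taken on only some, say which. Note that a paper reading may differ from pH at capture: the module may be recovered up to 96 h after ingestion and prepared up to 24 h after collection. The documents give no figure for any such change, so this version is best reported beside the primary result and not in its place.
2. **Bounded conclusion.** State that meeting the primary endpoint shows recovery of a visually intact, sufficiently filled module. Base any claim of small-intestinal sampling on pH together with the planned paired 16S, qPCR and metabolomic comparison with stool.
3. **Supportive origin and contamination check.** Report that paired comparison next to the primary result for the one sequenced module per volunteer. Do not use it to reclassify volunteers: an unsequenced back-up could still satisfy the one-of-three rule, so the volunteer's status would be undetermined. Do not drop modules from the module–stool comparison because they resemble stool, which would make that comparison circular.

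The cost is some wording and a small added analysis, with no new assay. The downside is that the success proportion the trial can support may be lower, and the molecular check covers only one module per volunteer.

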
### 1.2. Medical Device Description

The Medical Device (MD) is developed to specifically target the small intestine, and it is designed to be easily recovered from faeces. It is a porous polymer protected by two walls. The outermost layer is gastro-resistant, in the form of a size 00 gastro-resistant pharmaceutical capsule. This capsule is produced by Lonza Capsules & Health Ingredients (Colmar, France) and targets the distal parts of the small intestine [40]. This enables the capsule to pass through the stomach without being damaged. The outer wall (capsule) then degrades once it reaches the distal jejunum/proximal ileum. The MD contains tree modules, allowing for the multi-sampling of the small intestinal liquid. These modules are radio-opaque, allowing for the location of the MD in the GIT, if needed, using an X-ray or a scanner. The device is designed in compliance with medical device design standards, using biocompatible, certified materials and has no electronic materials or energy sources, thus limiting production risks and costs. 

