### 2.5. Clinical Study Protocol

During the screening visit, which takes place about a week before the inclusion visit at the hepato-gastroenterology department, the investigator informs the volunteer and answers any questions about the objective, the nature of the constraints, the foreseeable risks, and the expected benefits of the study. The investigator also explains the volunteer’s rights in a clinical trial and outlines the eligibility criteria. 

After receiving this information, volunteers are given at least 24 h to consider their decision to participate in the study or not. If, after the reflection period, the volunteer does not wish to give consent, he or she simply informs the research team by telephone or e-mail.

Once included in the study, on the appointed day, the volunteer comes to the hospital in the morning after a 10 h fasting to swallow the MD with 150 mL of water under the supervision of the study gastroenterologist. For women of childbearing potential, a pregnancy test is performed to exclude a pregnancy. After ingesting the MD, the volunteer must then wait 2 h before drinking and 4 h before eating. Consequently, the volunteer collects each faeces until the clinical study assistant calls him to stop the collection once all modules have been collected. For the faeces collection, the volunteer uses a special device named Fecotainer that can be placed directly in the toilet bowl. The collected sample must only contain faecal matter (no urine or blood) to be analysed. After defecation, the fresh sample is directly placed by the volunteer in a refrigerated place, and a biological transporter collects the sample from volunteer’s house to the hospital 24/7. Depending on the delivery hour at the hospital, the sample is directly prepared (from 8 h to 18 h) or placed at +4 °C (from 18 h to 8 h). Samples must be prepared in the next 24 h after collection and must be stored at +4 °C. The volunteer keeps track of their nutrition and sensation (presence or absence of pain, etc.) during study duration on a daily basis. 

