The sample preparation consists first in screening for the module in the collected faecal matter. If no module is detected, the faeces collection continues. If at least one, or all modules, are detected in the collected faecal sample, the modules are recovered. The collected modules are then washed and assessed (e.g., observed leakage), weighted (to estimate the intestinal liquid volume sampled), and the content is recovered by centrifugation, leading to a sample that is divided into a pellet (bacterial content) and supernatant (intestinal metabolites). The supernatant is transferred into a new Eppendorf tube for metabolomic analysis, and its pH is measured using a pH paper indicator. The pellet is used for metagenomic analysis. For each volunteer, one module is used for multi-omics analysis, and the remaining ones (if any) are stored in the biological collection in case of a complementary analysis and as backup. If a module is contaminated by faecal matter due to leakage, the back-up module is used for the multi-omics analysis. Faecal samples are also collected from healthy volunteers and will be analysed by the same approaches as the intestinal content collected with the medical device. All samples are stored at −80 °C until analysis. 

For two volunteers, culturomics analysis will be performed if at least two out of the three modules per healthy volunteer are recovered and contain more than 50 µL, displaying no faecal contamination. The first retrieved module will be used for metagenomics and metabolomics analysis, and the second retrieved module will be used for culturomics analysis and will be directly placed in an anaerobic bag to preserve strictly anaerobic bacteria. The samples will be rapidly sent to the culturomics platform at +4 °C. In case the third module is contamination-free, it will serve as a back-up for analysis. 

The design of the study is illustrated in Figure 1.

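### A pH of 5 or more at recovery is consistent with intestinal sampling, but does not prove that no stomach liquid entered the device

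*Protocol article*

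**What the plan says.** Section 1.3 lists as secondary objective 4 "to verify that the MD opened in the intestine". The matching item in section 1.4 is the pH of the recovered contents, with this inference attached: "a measured pH ≥5 will prove that the MD did not sample stomachal liquid where the pH is lower". No other criterion in that section addresses where the device opened.

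Section 2.5 describes the measurement. Modules are found in the faeces, washed, assessed and weighed, and their content is centrifuged. Of the supernatant it says that "its pH is measured using a pH paper indicator". No other pH reading is described. On timing, section 1.4 counts a module as analysable if "it is found in the faeces within a 96-h period", and section 2.5 adds "Samples must be prepared in the next 24 h after collection and must be stored at +4 °C".

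On construction, section 1.2 says of the device: "It is a porous polymer protected by two walls". The outer wall is a gastro-resistant capsule meant to degrade in the distal jejunum or proximal ileum. The article does not explain the second wall, or whether a module closes once it has filled.

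**The concern.** The criterion turns a measurement of the final state into a statement about history. Whether stomach liquid was ever sampled depends on what entered the module, and when. The pH paper shows only the acid-base state of what is in the module at recovery. The two agree if the module holds liquid from one place and that liquid does not change. They can differ if some gastric liquid entered early and buffered intestinal liquid followed.

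Early failure of the outer wall is the event this criterion exists to detect, and partial gastric filling followed by mixing is the form of failure it detects least well. At stake is what objective 4 may conclude. As written, a module that took in some stomach liquid could be reported as proof that none was taken in. For a device in its first evaluation in volunteers, that statement would also support the comparison of intestinal content with faeces.

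**Working it through.** The article gives no derivation for the cut-off of 5, so there is no figure of its own to reproduce. Two checks apply.

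**1. Delay between ingestion and reading.** Inputs from the article: up to 96 h to recovery of an analysable module (section 1.4, taking ingestion as the start) and up to 24 h from collection to preparation (section 2.5). The sum is 96 + 24 = 120 h. The reading can therefore come about five days after ingestion.

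**2. How much gastric liquid a mixture can hold and still read pH 5.** All inputs here are assumptions; none is in the article:

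- gastric liquid is strong acid at pH g, with g from 1 to 3
- intestinal liquid is at pH 7 with bicarbonate B from 5 to 60 mM and pKa 6.1
- the system is closed, so CO2 is retained

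Let f be the gastric volume share and A = 10^(−g) the acid concentration. Charge balance in the mixture at pH 5 is

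B(1 − f) − fA + 10^(−5) = C(1 − f) × Ka/(Ka + 10^(−5)),

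where the hydroxide term is negligible and C = B(1 + 10^(6.1−7)) = 1.126B is total carbonate. The bicarbonate fraction at pH 5 is 7.94×10^(−7)/(1.079×10^(−5)) = 0.0736. The right side is therefore 0.083B(1 − f). Solving, with concentrations in mM:

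f = (0.917B + 0.01)/(A + 0.917B).

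Worked ends of the range:

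- g = 1 (A = 100), B = 5: f = 4.60/104.59, about 4%.
- g = 3 (A = 1), B = 60: f = 55.04/56.03, about 98%.

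Largest gastric share that still reads pH ≥5:

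| Gastric pH | B = 5 mM | 15 mM | 30 mM | 60 mM |
|---|---|---|---|---|
| 1 | 4% | 12% | 22% | 36% |
| 1.5 | 13% | 30% | 47% | 64% |
| 2 | 32% | 58% | 73% | 85% |
| 3 | 82% | 93% | 97% | 98% |

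An unmixed gastric sample (f = 1) keeps its own pH of 1 to 3 and reads below 5. The rule therefore separates a purely gastric sample from an intestinal one. In every mixed case in the table it lets some gastric share through, and how much depends almost wholly on inputs the article does not give.

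**The case against.** The strongest reply is that a false pass needs two events: gastric entry, and then mixing or exchange with intestinal liquid. The article does not show that the second can happen. Section 1.2 mentions two walls and explains only one. The visual check in section 1.4 looks for damage that could let faeces in, and section 2.5 attributes contamination to leakage. That language treats an intact module as a container that keeps its contents separate. If a module closes after filling, a purely gastric fill would stay acidic and criterion 4 would catch it. This stands as a limit. A reader might infer from the porous polymer, and from the lack of any described closure, that modules exchange liquid freely during transit. A condensed article that leaves out the closure design does not support that inference. Partial filling before closure also remains possible, however, so the limit does not restore proof.

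It also stands that the percentages are not a property of this device. At gastric pH 1 the tolerated share is only 4% to 36%, so in part of the range the rule does detect substantial gastric filling. The 10 h fast and the exclusion of volunteers on medication make a high gastric pH at ingestion less likely. Neither bears on later buffering.

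A reader might also infer the opposite error: bacteria in the module form acid, and intestinal liquid is then read as gastric. The planned culturomics does not show this, and the article has no information on pH drift. The point should not be made.

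**Conclusion.** The inference in criterion 4 is stronger than the measurement described can support. A pH of at least 5, read up to about 120 h after ingestion, argues against a purely gastric, unmixed sample. It does not exclude earlier partial gastric entry. This rests on the timing and handling stated in sections 1.4 and 2.5, and on there being one reading, which is inferred because only one is described. The 4% to 98% range rests on assumed chemistry and on a module that does not close before intestinal liquid enters. It shows that the conclusion does not follow; it does not estimate how often it would be wrong.

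A reader might go further and infer that the device opens in the stomach, or that the main result is in doubt. The documents support neither. pH is not part of the definition of an analysable module, so the 12-of-15 rule is unaffected. Section 2.8 makes the secondary objectives descriptive apart from the multi-omics analyses, and no success count is set for pH. What changes is the conclusion that may be drawn for objective 4.

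**What to change.** In section 1.4, criterion 4, replace the inference with: *a measured pH ≥5 is consistent with intestinal content at recovery and does not by itself exclude earlier gastric entry*. Report objective 4 as supported, not proved. List each pH beside the time from ingestion to reading. If evidence exists on module closure and on pH stability over transit and storage, cite it, since that is what could justify a firmer statement.

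If bile acids are measured in the LC-MS/MS run already planned on one module per volunteer (sections 2.5 and 2.6), they may be shown beside pH as descriptive evidence of intestinal contact. Section 3 names conjugated primary bile acids as specific to the small intestine. They should not become a pass rule. A mixed gastric and intestinal sample would contain them too and would pass, and the modules held as backup would have no result to classify.

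The cost is a change of wording and one extra column in a listing, with no new sample, visit or participant. The downside is that objective 4 can no longer be reported as proved.
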